## Abstract

**Background:**

Patients with severe and enduring eating disorders (SEED) are seriously ill and have a low quality of life. Case management (CM), originally developed for adult patients with severe mental disabilities, has been shown to enhance social functioning and improve quality of life, while reducing the number and length of hospitalizations. In 2014, a special unit based on CM, for patients with SEED (the Eira unit) was started at Stockholm Centre for Eating Disorders, Sweden.

**Method/Design:**

This study aims to investigate if CM can improve SEED patients’ quality of life, and reduce their eating disorder symptoms as well as their health care consumption. Methods for data collection are a semi-structured diagnostic interview, self-report questionnaires, and a qualitative interview. The diagnostic interview and the self-report assessments will be done at start of treatment and at follow-ups after 1, 2, and 3years. The qualitative interview will be conducted 1 year after start of treatment. The study is approved by the ethical review board in Stockholm in compliance with the Helsinki Declaration.

**Discussion:**

CM is a possible new contribution to the treatment methods for SEED. It does not aim at remission, but rather to accept life as it is, and to enhance quality of life in the presence of the ED. This study will investigate the potential benefits of this novel intervention in a special unit for SEED patients.

**Trial registration:**

Clinicaltrials.gov Id: NCT02897622

## Background

Patients with eating disorders (ED) are a challenge for the health care system and the recovery from ED is often slow. Despite massive effort some of the patients do not recover and go on to develop a severe and enduring eating disorder (SEED). Patients with SEED have had an ED for a long time and have often undergone numerous treatments, either voluntarily or compulsory, without recovering from the ED. Owing to the nature of the ED the SEED patients remain seriously ill with severe distress due to social impairments, physical strain and psychiatric symptoms such as anxiety, depression and compulsiveness [1–3]. It is also common that relatives are affected, not only by constant concern, but also because the SEED leads to financial problems that family members have to deal with [4]. Many patients with SEED need long-term sick leave and are heavy consumers of health care, often with long in-patient somatic and psychiatric admissions [2, 5]. SEED patients often feel great and complicating ambivalence towards treatment [6]. Taken together these factors can contribute to a low motivation for treatment, which probably leads to a vicious circle that further complicates treatment and rehabilitation [5]. In the ED field, there is a growing consensus that treatment of patients with SEED needs to be multi-professional, with a focus on improving the patients’ social situation, minimizing medical complications, and enhancing quality of life and independence, rather than focusing one-sided on symptom reduction [3, 7, 8]. It is important to set mutual, acceptable and realistic goals that can be achieved, to do this in collaboration with the patients, and to allow this process a long time [9, 10]. Quality of life for patients with SEED-AN is seriously affected [11] and is as low as the quality of life in severely depressed and schizophrenic patients [8]. Besides the personal suffering of patients and their families, SEED is also associated with high costs for health care and for society in general.

Case management (CM) is a method developed for adult patients with severe mental disabilities such as schizophrenia, other psychoses, personality disorders or serious addiction problems. CM has been shown to improve quality of life [12], enhance social functioning [10], promote ability to live as independently as possible by reducing the number and length of hospitalizations for the patients [13]. CM efforts are individualized and can vary in time from a few months to several years [10]. This study will investigate the potential benefits of such a CM intervention in a special unit for SEED patients.

### Specific aims

The aim of this study is to evaluate a CM model for patients with SEED. Specific questions that the study aims to explore are:

Does entering the CM program lead to:Improvement in patients’ quality of life?Reduction of patients’ ED symptoms?Reduction of patients’ health care consumption and costs?

## Method

### Intervention

At the Stockholm Centre for Eating Disorders in Sweden a new special unit for SEED (Eira) was established in 2014. The staff at Eira consists of one doctor (part time), one social worker and two psychiatry nurses with long experience of ED-treatment.

Before a patient is accepted at Eira, a networking meeting is held, in which the patient is encouraged to bring important people, like family members, remittent or others. Following this meeting, the decision is made whether the patient should be accepted or not.

During the first 5–6 sessions at Eira, the patient’s psychiatric, somatic and social condition is carefully assessed, as well as her/his medical history and previous treatment experiences. It is important for the case manager (i.e. the social worker or one of the nurses) to know the patient and her/his preferences and needs well, in order to be able to coordinate the different caregivers and authorities involved in the patient’s life. The clinical contact between case manager and patient mainly consists of supportive conversations. However, in the “clinical case management” model used in Eira, the case manager also has a treating role, for example by performing social training, somatic controls and family support. The patient’s needs and preferences guide the frequency, place and form of the meetings. Meetings may take place wherever it is deemed appropriate, some meetings may even be in the form of phone calls or text messages.

Another of the case manager’s tasks is to aid the patient in contacts with different authorities and, if necessary, to help with economic issues. It is also important to regularly monitor the patient’s somatic condition.

If the patient is temporarily in need of more intensive somatic or psychiatric care, the case manager can help to plan such an effort. During the period of more intensive care, the case manager maintains contact with the patient by visits and phone calls, and by participating in meetings with the temporary caregivers.

With the patients’ consent, relatives are invited to participate in the CM intervention. Information and support is offered relatives on an individual basis, this also includes underage children. Twice a year, there is also a lecture about the SEED condition for the relatives (without participation of the patients) at Eira. During the lecture participants can ask questions and discuss problems they encounter as SEED relatives.

There is no time limit for the CM intervention. The patient is offered support as long as he/she wants it, independent of degree of ED symptoms or medical condition.

### Participants

The Eira unit can manage 30 patients simultaneously, and all patients included in the CM intervention will be asked to participate in the study. Eira accepts patients who have been suffering from ED for at least 10 years and participated in at least three failed treatment efforts in specialized ED units. Since they have been ill for a long time and since previous treatment efforts have been unsuccessful, patients participating in the study will act as their own controls.

The study is approved by the ethical review board in Stockholm in compliance with the Helsinki Declaration.

### Measures

Methods for data collection are a semi-structured diagnostic interview, a qualitative interview, self-report questionnaires and data from medical records. The diagnostic interview and the self-report assessments will be done at start of treatment and at follow-ups after 1, 2, and 3 years. The qualitative interview will be conducted one year after start of treatment. Data from medical records will be collected retrospectively.

*The Structured Eating Disorder Interview (SEDI)* is a semi-structured diagnostic interview for ED diagnoses according to the DSM-IV. The interview consists of a maximum of 30 and normally about 20–25 questions [14].

*The RAND-36* (also known as the SF-36) measures health-related quality of life (HRQoL) [13]. Changes in the HRQoL over time can be seen by comparing repeated assessments [15, 16].

*The Eating Disorder Examination Questionnaire (EDE-Q)* measures central symptomatic aspects of ED by way of patient’s self-ratings [17, 18].

*The Treatment Satisfaction Scale 2* (*TSS-2*) is a patient-rated assessment of treatment satisfaction in a simple 6-item scale [19]. TSS-2 will be used at all follow-ups.

*The qualitative interview* is semi-structured and consists of three broad themes:The patient’s thoughts about her/his life situation in the year he/she has been at Eira.The patient’s thoughts and reflections about her/his quality of life, and whether it has been affected in the year he/she has been at Eira.The patient’s thoughts about her/his future.

The informants will be asked to talk openly around these themes. The interviewer, who is the same person for all interviews, is a psychologist who is not part of the Eira staff (Table 1).

**Table 1 Tab1:** Measures over time

Measure	Baseline	1 year	2 years	3 years
SEDI	X	X	X	X
RAND-36	X	X	X	X
EDE-Q	X	X	X	X
TSS-2		X	X	X
Interview		X		

### Outcome

Primary outcome is quality of life. Secondary outcomes are health care consumption and costs, and ED symptoms at 1, 2 and 3 years follow-up.

### Qualitative analysis

The interview will be tape-recorded and transcribed verbatim. After the interview the patients will have an opportunity to review a transcript and to evaluate and comment upon what has been said. The interviews will be analysed with qualitative content analysis according to Hsieh & Shannon [20].

### Evaluation of cost-effectiveness

The cost-effectiveness analysis consists of costs of the CM intervention, changes in quality of life, as well as societal costs such as health care usage and loss of production. The perspective of the analysis will be societal and the time horizon 3 years. The analysis method is going to be cost-utility analysis with health effect expressed in quality adjusted life years (QALY) [21]. The analysis will be complemented with the probability of acceptable cost-effectiveness with different willingness to pay for a QALY [22, 23].

All costs of the CM intervention occur at Eira. The cost for each patient in the study can be calculated by Eira’s total cost divided with each patient’s share of resource utilization based on enrolled time.

QALYs will be estimated based on RAND-36 transformed to SF-6D based on a British preference score [24, 25]. From the measures at baseline, and after 1, 2 and 3 years, changes in QALYs can be estimated. From medical records, changes in cost of health care usage can be calculated. The participants’ employment and change acquisition work rate is followed during the same period based on interviews with participants.

The treatment may also have impact on relatives’ quality of life, costs and earnings. These aspects will not be considered in the analysis.

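### The stated rule for a patient's intervention cost divides the unit's total cost by the patient's share, where it should multiply

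*Protocol article*

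**What the plan says.** The protocol article, Evaluation of cost-effectiveness, plans a societal cost-utility analysis over 3 years, with the probability of acceptable cost-effectiveness at different values of a QALY. On the intervention's own cost it says "All costs of the CM intervention occur at Eira". A patient's cost is then obtained from the unit's "total cost divided with each patient’s share of resource utilization based on enrolled time". The article gives no other formula for this cost and no cost figure.

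Three other places bear on the point:

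- Outcome lists costs, together with health care consumption, among the secondary outcomes; quality of life is primary.
- Participants states "The Eira unit can manage 30 patients simultaneously" and that all patients in the intervention will be invited into the study.
- Intervention describes a small fixed staff and says that each patient's "needs and preferences guide the frequency, place and form of the meetings".

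**The concern.** A share is the part of a whole that belongs to one patient. Apportioning a total means multiplying it by that part, so that the parts add back to the total. The article instead divides the total by the share. The result moves the wrong way: the smaller the share, the larger the cost.

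Since all intervention costs are said to arise at the unit, this sentence covers the whole intervention side of the cost-utility analysis. An analyst or replicator who followed it as written would carry meaningless patient costs into the cost per QALY and the acceptability probabilities. The QALYs themselves, and the primary outcome, would not be affected.

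**Working it through.** The article gives no cost figure to reproduce, so the check is algebraic, with illustrative shares.

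**Inputs.** T is the unit's total cost in the period, left as a symbol. The share of patient i is s = (patient's enrolled time) / (sum of enrolled time), because the article bases the "share of resource utilization based on enrolled time". The number 30 is the unit's simultaneous capacity (Participants). It is not a stated sample size and serves only as an illustration. The enrolment times of 12, 24 and 36 months in step 2 are assumed.

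**Rules compared.** As written: cost = T / s. Apportionment: cost = T × s.

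**Step 1: 30 equal shares, s = 1/30.**

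- As written: T / (1/30) = 30 T per patient; sum over 30 patients = 30 × 30 T = 900 T.
- Apportionment: T × 1/30 = 0.033 T per patient; sum = T.
- Ratio per patient: 30 / (1/30) = 900.

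**Step 2: unequal enrolment, 10 patients each at 12, 24 and 36 months.** Total time = 10 × (12 + 24 + 36) = 720 months.

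| Months enrolled | Share s | As written, T / s | Apportionment, T × s |
|---|---|---|---|
| 12 | 12/720 = 0.0167 | 60 T | 0.0167 T |
| 24 | 24/720 = 0.0333 | 30 T | 0.0333 T |
| 36 | 36/720 = 0.05 | 20 T | 0.05 T |
| Sum over 30 patients | 1 | 10 × (60 + 30 + 20) T = 1100 T | 10 × (0.0167 + 0.0333 + 0.05) T = T |

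As written, a patient enrolled for 12 months costs three times as much as one enrolled for 36 months. Apportionment gives one third.

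**Step 3: any share.** For every s below 1, T / s is greater than T. The literal rule therefore charges each patient more than the whole unit costs, whatever the number of patients or their enrolment. This conclusion does not depend on the illustrations.

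**Step 4: does the choice of enrolled time add a second error?** Suppose that patients with equal enrolled time used resources in the ratio 0.5, 1 and 2, with 10 patients each (assumed). The weights sum to 10 × 3.5 = 35. Costs in proportion to use would be 0.5 × 30/35 = 0.43, 1 × 30/35 = 0.86 and 2 × 30/35 = 1.71 times the uniform time-based cost. The mean is (0.43 + 0.86 + 1.71) / 3 = 1.00 times that cost. If all the unit's patients are in the study, time-based allocation therefore leaves the total and the mean unchanged. Only the spread between patients, and its relation to QALYs, differs.

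**The case against.** The strongest reply is that this is a slip of language. A sentence about a patient's share of resource use makes sense only as apportionment, other sentences in the article are also awkward in English, and an analyst would notice a patient who cost more than the whole unit. This stands. The 900-fold figure describes the literal reading only and is no forecast of an error in the results. The reply does not remove the point, because the article chose to state a formula, the formula is wrong, and no other is given. Leaving detail to a fuller plan would explain an omission; it does not explain an incorrect rule.

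A reader might go further and infer that allocation by enrolled time is also an error, since contacts are individual and "some meetings may even be in the form of phone calls or text messages". The document does not support this. For a small unit with fixed staff and a fixed number of places, spreading the cost over place-time is a coherent top-down method, and step 4 shows no shift in the mean if all the unit's patients take part. The mean for participants could shift only if they differ in intensity from patients who decline.

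A reader might also infer that time-only shares make the uncertainty in the acceptability analysis too small. With an assumed coefficient of variation of 0.5 to 1.0 in contact intensity and 30 patients, the standard error of mean intervention cost would be 0.5/√30 = 9% to 1.0/√30 = 18% of the mean. But the coefficient of variation is assumed, 30 is capacity, and this is one cost component only. The variance of net benefit at willingness to pay λ is λ²Var(Q) + Var(C) − 2λCov(Q,C), where Q is QALYs and C is cost. If heavier contact goes with larger QALY gains, adding patient-level variation can lower it. The article gives neither the sign nor the size of that covariance.

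Finally, it is tempting to call the intervention the main incremental cost. The article has no cost figures, and health care use and production loss also enter the analysis, so that ranking has no source.

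**Conclusion.** The costing rule is wrong as written and should be corrected. For any share below 1 it gives each patient more than the unit's total cost, reverses the order of patients by enrolled time, and does not sum to the total. That rests on algebra alone; the factor of 900 additionally assumes 30 equal shares and a literal reading. The practical size is that of a formula correction for a secondary outcome, because the intended meaning is probably apportionment and nothing shows that costs will be miscalculated. Allocation by enrolled time is an acceptable choice and is not part of the error.

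**What to change.** Replace the sentence with: *patient cost = the unit's total cost in the period multiplied by the patient's share of total enrolled time in that period, with shares taken over all patients of the unit, participants or not, and summing to 1.* Taking shares over all patients matters because patients are only asked to join the study; shares over participants alone would load the cost of non-participants onto them. This is one sentence and costs nothing.

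Optional: state as a limitation that enrolled time does not capture differences in contact intensity, or vary the allocation in the sensitivity analysis, which the Discussion currently directs at health care use and production costs. The second option depends on whether contact type and duration are recorded. The article does not say so, and the extra work cannot be judged from it.

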## Discussion

The treatment of patients with SEED often causes frustration and confusion among ED clinicians, since these patients often have tried “everything” without a lasting positive effect. In our clinical experience this often results in a situation where patients are considered “unmotivated” and dismissed from treatment, which in turn often leads to a symptom deterioration and that patients eventually return to the clinic in need for more acute interventions. As an alternative, clinicians may continue to offer patients interventions that neither therapist nor patient believes is helpful – at least not in a longer perspective. It might be time to re-evaluate what a positive outcome is for these patients.

CM provides an alternative to traditional treatment aiming at symptom reduction. CM aims to improve the patients’ quality of life, enhance their social functioning, and promote their ability to live as independently as possible despite their illness. CM offers unconditional long-term support, without requiring treatment progress. Instead CM stresses stabilization and harm-minimizing interventions, which are assumed to both increase quality of life and social functioning and to reduce the number and length of hospitalizations.

There has been no similar service for patients with ED in Sweden or, to our knowledge, anywhere else. For a long time, CM has been used for patients with serious mental disabilities, such as schizophrenia, other psychoses or personality disorders, as well as for serious substance abuse problems. Since previous studies have shown similarities between SEED patients and patients with schizophrenia [2], it is reasonable to think that CM can be helpful also for SEED. However, we stress that CM is not an intervention for patients with a short duration of illness. For these patients, full recovery should be the main focus. It is also important to point out that CM is not to be seen as a “last resort” or as palliative care. The patients’ goals, life situation and abilities must always be the guiding principle in any intervention, and an important task for the case manager is to always keep an open dialogue with the patients. Although the patients previously have not had a lasting effect of any treatment interventions, this is never to be seen as a “failure”. At another time, in another life situation, the conditions may be better. One of the case managers’ tasks is to guide and help the patients to get access to the right intervention at the right time, and to create the best possible conditions for this intervention.

The primary outcome of this study is quality of life, which will be measured with both quantitative and qualitative measures. It is important to learn more about how SEED patients define quality of life. Is it to have fewer ED symptoms? Better economy? Or is it to be at peace with the ED, without the risk of becoming somatically too ill? Secondary outcome measures are ED diagnosis, ED symptoms, treatment satisfaction and health care consumption. In terms of ED diagnosis, there is no goal of remission with the support of CM. However, it is important to monitor any changes in ED diagnosis and symptoms over time.

The patients’ acceptance of CM at Eira will also be followed up with both quantitative and qualitative measures, to gain an understanding of the patients’ thoughts about the intervention. Perhaps CM will impact the SEED patients’ positively, but there is also a risk that patients will feel more vulnerable and alone when active treatment to reduce symptoms or pushing for weight gain is terminated.

The entire study is uncontrolled and compares conditions before and during the intervention based on an assumption that no changes would occur without the intervention. This assumption creates uncertainty and the sensitivity analysis is therefore particularly important. Especially sensitive to external influences are healthcare usage and productions costs will be considered. They can be affected by changes in the health care organization, enrolment principles and changes in the labour market. Therefore, these conditions will be specifically studied, and in the sensitivity analysis cost-effectiveness will also be estimated without those possible benefits.

In summary, it is our hope that CM, despite its seemingly limited ambitions, will prove to improve living conditions for SEED patients as well as to reduce society’s cost.

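### Health care use (aim 3) is judged against a single "before" level assumed to persist, although the planned record review could test that assumption with each patient's own multi-year history

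*Protocol article*

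**What the plan says.** All of the following is in the Protocol article.

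- **Aim.** Specific aims asks whether entering the programme leads to "Reduction of patients’ health care consumption and costs". The Outcome section lists this as a secondary outcome.
- **Comparator.** Under Participants, "patients participating in the study will act as their own controls", justified by long illness and unsuccessful earlier treatment. The Discussion states the premise: the study "compares conditions before and during the intervention based on an assumption that no changes would occur without the intervention".
- **Data.** Under Measures, "Data from medical records will be collected retrospectively". Evaluation of cost-effectiveness adds that changes in the cost of care can be worked out from those records. The article gives no length for the pre-entry period.
- **History available.** The entry criterion under Participants reads: "suffering from ED for at least 10 years and participated in at least three failed treatment efforts in specialized ED units".
- **Course of care.** The Discussion says that dismissal from treatment often "leads to a symptom deterioration and that patients eventually return to the clinic in need for more acute interventions".
- **Safeguards.** The Discussion concedes that the no-change assumption creates uncertainty. It says that outside conditions (care organisation, enrolment, the labour market) will be studied, and that "in the sensitivity analysis cost-effectiveness will also be estimated without those possible benefits".

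**The concern.** Long illness and repeated treatment failure make spontaneous recovery unlikely. They do not make yearly care use stable. A patient can remain ill for a decade while admissions and contacts rise and fall, and the Discussion describes that kind of course. The level read near entry then need not be the level that would have continued. If entry tends to follow a spell of heavy use, the later fall back to the patient's usual level looks like a saving. If it tends to follow a spell out of care, a true saving is masked.

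Care use is also the outcome for which the premise is easiest to check. In the article's Table 1 the quality-of-life and symptom questionnaires begin at baseline, so they have no pre-entry history. Records do. A conclusion about reduced consumption, and the cost side of the cost-utility analysis, depend on the answer.

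**Working it through.** The article states no sample size, variance, effect size or rate of care use, so there is no figure to reproduce. The check has four steps.

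**1. Does the stated sensitivity analysis answer aim 3?** Write ΔC for the change in care cost and ΔP for the change in production cost. The main analysis uses ΔC and ΔP as observed. The alternative run leaves both out, in effect setting ΔC = ΔP = 0. That protects the cost-effectiveness conclusion against relying on doubtful savings. It does not estimate ΔC, which is what aim 3 asks about.

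**2. How does an untypical entry year act?** This illustration rests on assumptions that are not in the documents. There is no true effect. Yearly use varies around the patient's own level with within-patient SD 1 and year-to-year correlation ρ. The last pre-entry year lies k SD from that level (k > 0 a peak, k < 0 a trough). "After" is the mean of 3 years. The expected apparent fall is:

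- last year as baseline: k × [1 − (ρ + ρ² + ρ³)/3]
- mean of 5 pre-entry years: k × [(1 + ρ + ρ² + ρ³ + ρ⁴)/5 − (ρ + ρ² + ρ³)/3]
- years 2 to 5 before entry: k × [(ρ + ρ² + ρ³ + ρ⁴)/4 − (ρ + ρ² + ρ³)/3]

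| k = 0.5 | ρ = 0.2 | ρ = 0.5 |
|---|---|---|
| Last year | 0.5 × (1 − 0.083) = 0.46 | 0.5 × (1 − 0.292) = 0.35 |
| 5-year mean | 0.5 × (0.250 − 0.083) = 0.08 | 0.5 × (0.388 − 0.292) = 0.05 |
| Years 2 to 5 | 0.5 × (0.062 − 0.083) = −0.01 | 0.5 × (0.234 − 0.292) = −0.03 |

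A simulation with the same assumptions agrees (0.47 and 0.36; 0.09 and 0.05; −0.01 and −0.02). Every entry is proportional to k, so k = −0.5 reverses each sign and a real saving is understated. The article gives neither the sign nor the size of k.

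**3. Is the earlier-years baseline always safer?** No.

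- Patients must have had at least three failed specialised treatments, so earlier years may themselves be selected for high use. With ρ = 0, if each of years 2 to 5 lies h SD above the patient's level and the entry year does not, the earlier-years baseline is wrong by h and the entry-year baseline by 0.
- A natural decline also matters. Number the pre-entry years −5 to −1 and the three later years 0, 1, 2 (mean 1). Years −5 to −2 have mean −3.5, a gap of 4.5 years; the last pre-entry year has a gap of 2. At an assumed decline of 0.05 SD per year, the false fall is 4.5 × 0.05 = 0.225 SD against 2 × 0.05 = 0.10 SD.

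The pre-entry level and trend therefore have to be shown, and both baselines reported.

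**4. Can calendar time be adjusted for as well?** Calendar year equals entry date plus time since entry, so full sets of patient, relative-time and calendar-year effects are linearly dependent. A trial design matrix for 30 patients with staggered entry had rank 46 for 47 columns. Pooled periods or another stated restriction are needed.

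**The case against.** The strongest reply is that the article discloses the weakness, names external influences, says they will be studied, and adds a conservative cost-effectiveness run. It is a condensed account: the full protocol may fix a multi-year look-back, and nothing in the article rules one out. This stands in part. The absent window is not the finding, and it would be wrong to say that deleting the savings is the only safeguard. But neither stated step yields an estimate of the change in care use that allows for fluctuation within patients around entry.

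A reader might infer more than the text supports:

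- **That patients enter at a peak.** The entry criteria are long illness and failed treatments, not an acute episode. The Intervention section mentions only a meeting that the referrer may attend. The Discussion describes these patients' care in general, and also a second path in which interventions simply continue. A recently dismissed patient could enter at low use.
- **That "before" means one year.** No section says so.
- **That a false-positive rate can be attached to the plan.** Simulations under no effect give high rates of spurious reductions with an entry-year baseline, but sample size, variances, correlation and strength of selection are all assumed. The only size given is capacity ("The Eira unit can manage 30 patients simultaneously"), and the article states no significance test for care use. Such results show direction only.

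**Conclusion.** The point holds as a cheap improvement to the analysis of a secondary outcome. The no-change premise is explicit, the article's own account of the care course does not fit it for health care use, and the stated safeguards do not repair the estimate that aim 3 needs. The bias could run either way. Its size cannot be derived from the documents; the 0.35 to 0.46 SD in the working applies only if a single entry year is the baseline and lies 0.5 within-patient SD from the patient's usual level. The conclusion rests on the stated assumption set against the described course, not on any missing detail. It does not extend to the questionnaire outcomes, for which the article plans no pre-entry measurements.

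**What to change.** Amend the article's Evaluation of cost-effectiveness section and the closing part of its Discussion (or the full protocol behind them) as follows.

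1. From the record review already planned, build a patient-year series of care use over a fixed pre-entry period, for example 5 years, and the 3 years after entry.
2. Show the last 12 months before entry as a separate period, so that a peak or a trough is visible. Report the pre-entry level and trend as a direct check of the no-change assumption.
3. Estimate the change against the pooled earlier pre-entry years, with patient effects. Give the result with the entry year included as a sensitivity analysis, since the failed-treatment criterion may raise use in earlier years.
4. If calendar time is adjusted for, use pooled periods or another stated restriction. Do not fit full patient, relative-time and calendar-year effects together.
5. Carry the estimate and its interval into the cost-utility analysis, and keep the run without care-use and production benefits as the bound.

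The cost is a longer look-back for roughly 30 patients and one model, with no new visits or questionnaires. Older records may be incomplete, and the reported saving will probably be less favourable or less precise.
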